## Abstract

**Background:**

Patients, identified to be at risk for but who have never experienced a potentially lethal cardiac arrhythmia, have the option of receiving an implantable cardioverter defibrillator (ICD) as prophylaxis against sudden cardiac death - a primary prevention indication. In Canada, there is no clear framework to support patients’ decision-making for these devices. Decision support, using a decision aid, could moderate treatment-related uncertainty and prepare patients to make well-informed decisions. Patient decision aids provide information on treatment options, risks, and benefits, to help patients clarify their values for outcomes of treatment options. The objectives of this research are: 1) develop a decision aid, 2) evaluate the decision aid, and 3) determine the feasibility of conducting a trial.

**Methods/design:**

A development panel comprised of the core investigative team, health service researchers, decision science experts, cardiovascular healthcare practitioners, and ICD patient representatives will collaborate to provide input on the content and format of the aid. To generate probabilities to include in the aid, we will synthesize primary prevention ICD evidence. To obtain anonymous input about the facts and content, we will employ a modified Delphi process. To evaluate the draft decision aid will invite ICD patients and their families (n = 30) to rate its acceptability. After we evaluate the aid, to determine the feasibility, we will conduct a feasibility pilot randomized controlled trial (RCT) in new ICD candidates (n = 80). Participants will be randomized to receive a decision aid *prior* to specialist consultation *versus* usual care. Results from the pilot RCT will determine the feasibility of research processes; inform sample size calculation, measure decision quality (knowledge, values, decision conflict) and the influence of health related quality of life on decision-making.

**Discussion:**

Our study seeks to develop a decision aid, for patients offered their first ICD for prophylaxis against sudden cardiac death. This paper outlines the background and methods of a pilot randomized trial which will inform a larger multicenter trial. Ultimately, decision support prior to specialist consultation could enhance the decision-making process between patients, physicians, and families, associated with life-prolonging medical devices like the ICD.

**Trial registration:**

ClinicalTrials.gov: NCT01876173

## Background

Sudden cardiac death due to ventricular tachyarrhythmia is a serious cause of cardiovascular death in Canada [1], Europe [2,3], and the United States [4]. An innovative cardiovascular intervention to reduce the incidence of sudden cardiac death is the implantable cardioverter defibrillator (ICD). To restore a normal heart rhythm, the ICD delivers an internal shock, or anti-tachycardia pacing via an internally placed cardiovascular lead attached to the right ventricle of the heart. Evidence from randomized controlled trials (RCTs) and systematic reviews has demonstrated the effectiveness of ICDs for improving mortality and morbidity outcomes in patients with ischemic and non-ischemic disease, and heart failure [5-14]. Clinical practice guidelines provide current risk criteria to guide patient ICD candidacy [15]. Patients with or without ischemic disease, and reduced left ventricular function (among other criteria) may be offered an ICD for a primary prevention indication or sudden death prophylaxis. In addition, patients with heart failure may also be eligible for an ICD with the option of cardiac resynchronization, to augment ventricular efficiency and output [16]. Furthermore, indications for ICDs are broadening to include prophylaxis for genetically inherited channelopathies such as long QT-syndrome [16]. Estimates of the number of eligible Canadians range from 85,000 to 92,000 [16,17], with 3,700 candidates accruing annually.

Specialized electrophysiologists navigate the evidence associated with device options and risk-stratify their patients. However, for the patient and their families, the decision to receive an ICD may not be straightforward. Additional complexities surrounding ICD implantation, benefits, complications, and delivery of therapy exist, which warrant special attention to prepare patients to make informed, value-based choices. ICDs have benefits and risks associated with implantation, replacement, advisories, and psychosocial adjustment during the ICD lifetime [18-22]. These complex factors, balanced with the presence of competing mortality risks warrant structured, evidence-informed decision support. Decision support using a patient decision aid (PtDA) can moderate decisional conflict or treatment uncertainty and is used successfully in practice among several health treatment situations to improve patient outcomes [23]. A PtDA uses informational documents, or visual aids designed to *prepare* patients for decision-making about treatment options. Decision aids are intended to supplement rather than replace counselling from practitioners [24]. They are not passive informed consent materials, or educational interventions that are not geared to a specific decision. A 2011 Cochrane review of 86 studies found that when patients use decision aids they: a) improve their knowledge of the options; b) are helped to have more accurate expectations of possible benefits and harms; c) reach choices that are more consistent with their informed values; and d) participate more in decision making [23]. To date, the effectiveness of decision aids use in cardiovascular patients has been tested in atrial fibrillation [25,26], ischemic heart disease [27], and angiography [28,29]. To our knowledge, there is no research evaluating the use of a PtDA in patients who are offered an ICD for prophylaxis against sudden cardiac death in Canada.

Decision aids are used when there is more than one option. In the context of ICDs, this entails a choice between an elective prophylactic intervention versus continued optimal medical management - not *death,* but an *annual risk* of an arrhythmia. However, candidates who live with advancing heart failure may not comprehend the implications of living longer with their heart failure or the risks associated with ICD therapy if device shocks are received. At the point of decision-making for life-prolonging interventions, provision of time to consider end-of-life decisions may seem to be a contradiction. Nonetheless, this conversation and an introduction to what will be a future health decision are entrenched in the choice to receive an ICD [30]. Decision aids are embedded within the framework of shared decision-making, wherein together, patient, families, and physicians reach agreement on treatment-related decisions [31]. This approach stems from the concept of patient centered care [32]. In essence, shared decision-making encourages *active* engagement of patients during the process of decision-making and decision aids facilitate their participation. We have identified a need to provide better decision support for ICD patients during their decision-making process [30].

A considerable body of evidence gathered from ICD recipients suggests that psychosocial factors, including depression [33], anxiety [34-37] and personality [38,39] are associated with patient reported outcomes. Patients who receive shocks from the ICD report reductions in health-related quality of life (HRQL) [40,41]. Furthermore, the prevalence of depression or depressive symptoms is high both pre-ICD implantation and post-ICD implantation [42]. The influence of these factors at the time of health care decision-making is not known. We previously reported a high prevalence of depressive symptoms pre-implantation (30%), accompanied by poor pre-implantation mental-HRQL [43]. Poor mental-HRQL had a significant influence on early ICD acceptance in participants. This work highlights patient-specific factors known to influence patients’ HRQL, acceptance of, and adjustment to living with an ICD. Furthermore, a standard ICD does not alter or improve a patient’s underlying cardiovascular condition or symptoms. However, an ICD with added cardiac resynchronization (CRT) has a greater likelihood of improving heart failure symptoms and HRQL due to its ability to restore synchrony of the ventricles [11]. Differentiating what an ICD can and cannot do is vital for patients to consider at the time of decision-making.

### Conceptual framework

The Ottawa Decision Support Framework (ODSF) [44] provides the conceptual framework for this research. The ODSF is rooted in evidence, concepts, and theories from psychology, decision analysis, decisional conflict, values, and self-efficacy [45]. Importantly, the ODSF emphasizes decision *preparation* using a framework that separates the effects of each decision support method [44]. The framework has three main elements (decisional needs, decision support, and decision quality) [45]. The framework asserts that participant’ decisional needs (perceptions of the decision, knowledge, unrealistic expectations of outcomes, uncertainty, values, support, and resources, personal and clinical characteristics), affect decision quality. Decision quality is defined as reaching a decision that is based on the best available evidence and patients’ informed values for outcomes of options. The second element; decision quality, affects behavior (for example, delays), health outcomes, emotions, costs, and use of services [45]. Clinical characteristics may include the health status of patients. The final element is decision support [45]. The aim of decision support when delivered through a decision aid, counselling, or coaching is to improve decision quality by addressing unresolved decisional needs. Treatment effects associated with decision support, framed within the ODSF have been empirically tested [44,46-51].

## Methods

To meet the objectives of this research, the study will take place in three steps using a combination of quantitative and qualitative methods. In step one, we will draft, assess, and revise the decision aid contents using an inter-disciplinary panel of health services researchers, educators, practitioners, and ICD patients. In step two, we will invite patients and their family members who are experienced with the decision (have an ICD) to review and give feedback on the draft PtDA. Modifications based on patient and family feedback, will be made if necessary. Step three will employ a feasibility pilot randomized controlled trial in a single center, employing 1:1 allocation. The study setting is Hamilton Health Sciences (HHS), an academic tertiary care centre in Hamilton, ON, Canada. The center serves over one point four million residents in the regions of Brant, Burlington, Haldimand, Hamilton, Niagara, and Norfolk for cardiovascular procedures.

### Step one: development of the decision aid

Development of the PtDA is guided by the ODSF and International Patient Decision Aid Standards (IPDAS) quality criteria [24,45]. Development includes, 1) synthesize evidence- based information about ICDs, 2) consider ways of presenting the ICD options (accepting or declining an ICD) ensuring good risk communication and addressing uncertainties, 3) determine the values associated with the benefits and risks that are important to patients, and 4) draft decision aid using a structured approach that can guide the patient through the decision-making process. In addition to IPDAS, development of the PtDA will be guided by components suggested in O’Connor and Edwards [52], and O’Connor and Jacobson [51].

A development panel comprised of the core investigative team, cardiovascular healthcare practitioners (heart failure, general cardiology, internal medicine, and nurse specialists), health service researchers, ICD patient representatives, and a decision aid expert, will collaborate to provide input on the information, content, and format of the aid. Early engagement of patient representatives and knowledge users is intentional as an integrated knowledge translation technique in order to build a foundation for effective knowledge translation and user uptake of the decision aid in a clinical context [53].

In order to inform the risk and benefit information for the ICD decision aid, the we will adapt and synthesize existing ICD practice guidelines, current meta-analyses of randomized trials, and systematic reviews specific to the primary prevention ICD indication population to develop probabilities to include in the aid [14,20,22,54-56].

The process of selecting final content to include in the ICD PtDA will include a survey using a Delphi process [57,58]. Electrophysiologists, nurses, decision science experts, stakeholders, and patients with ICDs will be invited to provide feedback on PtDA content. We will employ an electronic survey, utilizing confidential login procedures through a secure website administered at the study site. If requested by patient participants, anonymous paper versions will be provided. The Delphi process will seek to overcome some of the challenges found with making decisions in groups. The Delphi approach attempts to assess the extent of agreement and to resolve disagreement. The features include: 1) anonymity; achieved by use of a questionnaire, 2) iteration where the processes occur in ‘rounds’, 3) controlled feedback*,* showing the distribution of the group’s response, and 4) statistical group response using summary measures [57,58]. The process will take place in up to three rounds. Round 1: participants will be invited to provide opinions on the a) facts and information about ICDs, b) presentations of risks and benefits, and c) values clarification exercises, based on knowledge and experience. The opinions will be grouped under discreet headings drafted for circulation to all participants on a questionnaire; round 2*:* participants rank their agreement with statements that did not reach agreement in round 1; the rankings will be summarized and included in round 2. If agreement is not reached in round 2, the process will be repeated for a final round.

### Step two: preliminary acceptability testing in patients with ICDs

To ensure the decision aid is acceptable, simple to complete, and clearly formatted for patient use, we will use a convenience sample of 30 patients from HHS with ICDs (primary prevention indication), and family members involved with the decision, to review the PtDA. In 2011, HHS received approximately 362 new ICD patient referrals. We will invite patients who are within one to six months of receiving the ICD. These patients will have the requisite experience with making ICD-related decisions, critical for informed and comprehensive assessment of the acceptability, feasibility, and formatting of the decision aid [59]*.* Exclusion criteria include 1) inability to understand the decision aid due to a language or visual impairment or 2) unstable cardiac condition. During scheduled outpatient ICD clinics, a physician or nurse specialist who is part of the healthcare team will introduce the study to patients. Patients who agree will receive an information package in the mail or if preferred, face to face. Demographics and medical history will be collected from the patients’ medical record and acceptability measures completed (see below).

### Step two: decision aid acceptability outcomes

Participants will complete the Decision Support Acceptability Scale (DSTA). The tool is used frequently during decision aid development and preliminary evaluation [60]. The DSTA questionnaire is comprised of ten items addressing comprehensibility of the decision aid components, balance in the presentation of options, the amount of information, and overall suitability [60]. Responses will be reported descriptively in terms of proportions of positive or negative responses to each item. We will summarize patient and family member feedback, any issues for discussion or revisions will be brought to the development panel.

### Step three: feasibility RCT testing

#### Primary purpose

##### Feasibility

Guided by the Ottawa Decision Support Framework [45] and the UK Medical Research Council recommendations [61], we will employ a feasibility pilot RCT (see Figure 1).

**Figure 1 F1:**
[figure not shown]
Feasibility pilot randomized controlled trial.

Feasibility endpoints will focus on *processes* (referral, recruitment rates, successful delivery of the decision aid, randomization procedures, the monitoring of *resources* (budget), and study *management* (trial coordination, human resources) [62]. We will assess the proportion of patients who complete the decision aid, percent of missing data, and questionnaire completion rates. Criteria for assessing the success of feasibility on key process outcomes include: 1) participant recruitment rate of at least 80% of all eligible patients, 2) successful delivery and completion of PtDA in 80% of consented patients prior to specialist consultation, 3) percentage of patients who complete PtDA of at least 80%, and 4) questionnaire completion rate of at least 80%.

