### Feasibility methodology

#### Participants, setting, and sample size

Participants will be patients referred for consultation for *de novo* ICDs for prophylaxis against sudden cardiac death. Exclusions are: 1) unable to understand the decision aid due to a language barrier or visual impairment, and 2) referral for an ICD with cardiac resynchronization or secondary prevention indication. To assess the feasibility of a conducting a larger trial, we will enroll 80 patients (40 per arm) over 10 months. The sample size for this pilot trial was based primarily on feasibility considerations. This pilot RCT will inform the estimates of effect sizes and variance for a larger trial.

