### Baseline visit

Members of the healthcare team will introduce the study to patients after ICD candidacy is determined but prior to their consultation in which the decision may be discussed/made. Introduction of the study will take place by mail or phone after candidates are contacted by the health care team to confirm the consultation appointment. Following the introduction to the study, the research assistant (RA) will either mail patients a study package, or arrange to meet patients for a baseline visit prior to the specialist consultation visit. At the time of the baseline visit, the RA will review study procedures, and obtain written consent. Following consent, the RA will collect baseline demographics, medical history, heart failure classification (NYHA), HRQL, and depressive symptoms. Once complete, the RA will randomize the patient.

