### Usual care

The usual care group will receive standard HHS information upon arrival for their specialist consultation.

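### Feasibility criterion 2 puts its 80% threshold over consented patients, but only the decision aid arm gets the aid, so read literally it cannot exceed about 50%

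*Protocol article*

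**What the plan says.** Feasibility is the primary purpose of step three. In the protocol article, under Step three: feasibility RCT testing (the text after Figure 1), four process criteria for success are listed, each with an 80% threshold. Two concern the aid itself:

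- Criterion 2: "successful delivery and completion of PtDA in 80% of consented patients prior to specialist consultation".
- Criterion 3: "percentage of patients who complete PtDA of at least 80" per cent.

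Neither names a trial arm.

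Other sections fix who can count towards these figures:

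- Methods: a "feasibility pilot randomized controlled trial in a single center, employing 1:1 allocation".
- Participants, setting, and sample size: "we will enroll 80 patients (40 per arm) over 10 months".
- Baseline visit: "the RA will review study procedures, and obtain written consent". Baseline data follow, and then "Once complete, the RA will randomize the patient".
- Intervention, and Visit one - pre consultation: the aid is used and completed by the intervention group.
- Usual care: "The usual care group will receive standard HHS information upon arrival for their specialist consultation".

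**The concern.** The numerator and denominator of criterion 2 come from different groups. Only patients allocated to the PtDA can contribute a completion before consultation, while patients in both arms have consented. Under equal allocation about half of the denominator can never contribute.

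Criterion 2 is the only one of the four thresholds that tests delivery before the specialist consultation. The Discussion gives that timing as the reason the feasibility work matters for a later multicentre trial. If the rule is applied as worded, a pilot with flawless delivery would be reported as missing this criterion. If it is applied as probably intended, the report will use a denominator that differs from the published one and will have to explain why. It is better to settle this while the article still gives the trial status as enrolling.

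**Working it through.** **Inputs**

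| Input | Value | Source in the protocol article |
|---|---|---|
| Enrolled | 80 | Participants, setting, and sample size |
| Allocation | 1:1 | Methods |
| Threshold, criterion 2 | 80%, taken as at least 80% | Step three, text after Figure 1 |
| Order of events | consent, baseline data, randomisation | Baseline visit; Allocation |
| Arm given the aid | intervention only | Intervention; Usual care; Visit one |

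**1. Reproduce the stated arm size.** 80 × 1/(1 + 1) = 40 per arm, which agrees with the article. The sample size itself rests on feasibility, so there is no power calculation to reproduce.

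**2. Completions needed on the stated denominator.** 0.80 × 80 = 64.

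**3. Completions possible.** Only the 40 patients in the PtDA arm are given the aid, so the maximum is 40. The ceiling is 40/80 = 50%. That is 64 − 40 = 24 patients, or 80 − 50 = 30 percentage points, short of the threshold.

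**4. What the literal criterion would read at good performance.** The literal figure is the completion rate in the PtDA arm × 40/80.

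| Completion in PtDA arm | Literal criterion 2 |
|---|---|
| 80% | 40% |
| 90% | 45% |
| 95% | 47.5% |
| 100% | 50% |

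Any patient who consents but is not randomised enlarges the denominator and lowers these figures further.

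**5. Could chance imbalance rescue it?** The article does not say whether allocation is blocked. Assuming simple 1:1 randomisation, which allows the most imbalance, the probability that at least 64 of 80 patients are allocated to the PtDA is P(X ≥ 64), X ~ Binomial(80, 0.5), or about 3 × 10⁻⁸. It could not.

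**6. The criterion on the PtDA arm.** 0.80 × 40 = 32, so the rule becomes at least 32 of 40. Treating patients as independent, the probability of reaching 32 is about 0.11, 0.59 and 0.98 if the true completion rate is 70%, 80% and 90%. The rule can then be met and separates poor from good delivery. The same 32 completers would be 32/80 = 40% on the stated denominator.

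**7. Criterion 3 on the same denominator.** Every patient who completes the aid before consultation has completed it. Completions at any time are therefore at least as many as completions before consultation. If the latter reach 32 of 40, so do the former, and criterion 3 adds nothing.

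**The case against.** The strongest reply is that the intended meaning is plain. Delivery of the aid can only be judged in patients who are due to receive it, and the Intervention, Usual care and Visit one sections say who they are. Criterion 1 refers to all eligible patients, whereas criterion 2 does not say all consented patients. The article also condenses a full protocol that is not shown, and Figure 1 is not available. Either might give the denominator by arm.

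Much of this stands. The PtDA arm is the likely intention, and on that reading the criterion works. But consent precedes randomisation, so consented patients, without qualification, means both arms. Elsewhere the article names the intervention group when a measure is confined to it, as for values and for preparation for decision making. Here it does not. Nor is this a complaint about detail left to another document: a denominator is stated, and it conflicts with the allocation described in the same article.

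Three stronger readings are tempting, and the article does not support them.

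- **That the pilot is bound to fail a go/no-go rule.** No such rule is stated. The criteria sit among other process, resource and management endpoints. Data collection, management and analysis calls the feasibility analysis mainly descriptive, and nothing says that missing one criterion stops the larger trial.
- **That using the PtDA arm at analysis would amount to choosing a success rule after seeing the data.** The 80% figure would not move, and the arm that receives the aid is already defined in the article.
- **That criterion 3 has the same arithmetic fault.** It gives no denominator beyond patients and does not mention consent, so it is unclear rather than contradictory.

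**Conclusion.** The denominator of criterion 2 is wrong as written. The criterion asks for 64 of 80 where at most 40 of 80 (50%) can occur. On the PtDA arm it asks for 32 of 40 and can be met.

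This rests on three things stated in the article: consent comes before randomisation, arms are equal at 40 each, and usual care is not given the aid before consultation. It assumes that enrolment reaches 80 as planned. A different total changes the counts but not the ceiling of about one half.

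The severity is moderate. The fault lies in a stated success threshold for the pilot's primary purpose, but the intended group is easily inferred. The design, the comparisons between arms and the participants are unaffected.

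**What to change.** In criterion 2, replace the reference to consented patients with patients randomised to the PtDA arm, and give the count: at least 32 of 40 complete the aid before the specialist consultation.

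Confine criterion 3 to the PtDA arm as well, and then do one of the following:

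- Distinguish it from criterion 2, for example as completion at any time, or as completion among those to whom the aid was delivered.
- Merge it with criterion 2.

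If the full protocol already defines these denominators by arm, the article and the trial report need only be brought into line with it. The change is a few words. It needs no new data and no change to sample size or trial procedures, and it can be made before the feasibility results are analysed.
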